#### Education sessions

Concurrent with client recruitment, the study educator (in collaboration with the facility-based educator) will use 20-minute education sessions to train health care aides working day and evening shifts to complete the sit-to-stand activity. They will deliver these sessions a minimum of four times on participating units. The standardized education protocol (Additional file 1) was developed for this purpose by our education partner and evaluated by the research team. In brief, these interactive education sessions: 1) describe the benefits of the sit-to-stand activity for both clients and health care aides; 2) demonstrate the activity; 3) explain how the paper-based reminders will identify the clients participating in the activity; and 4) review documentation of client participation with the sit-to-stand activity using flowsheets. Health care aides will be taught (and expected by their employer) to prompt participating clients to slowly and repeatedly stand up and sit down on four occasions: twice on each day and evening shift. The number of repetitions on each occasion will vary with clients’ ability and fatigue. Health care aides will integrate the sit-to-stand activity into usual care routines (for example, while dressing or toileting) on two occasions during their shift.

#### Uptake monitoring

On the first day of the month following the completion of the education sessions, the manager or nurse in charge will announce the beginning of the sit-to-stand activity during report for the morning and evening shift changes. A list of participants posted at the shift change location will inform the health care aides about who is participating in the sit-to-stand activity. Aides will carry out the activity with participants in their care assignment, and record the number of sit-to-stands completed during each occasion on the flowsheet. Flowsheets for each participant will be collected at the end of every month. To optimize the fidelity of the innovation [42] leading to the secondary outcome measure (client mobility), we will monitor uptake and enhance the reliability of the health care aides’ flowsheet documentation for 2 months prior to randomization. First, the study educator will conduct two informal walkabouts with staff at each facility to discuss the activity and clarify any misconceptions. Second, on 3 days within the first week of each of the 2 months, a research assistant will review the documentation flowsheets by correcting and noting proper documentation style directly on the flowsheets. Third, a research assistant will conduct two documentation flowsheet information sessions at each facility, providing sample flowsheets and discussing with health care aides the correct documentation procedure.

### Randomization and client recruitment

A stratified blocked randomization procedure will assign facilities to intervention arms. Each of the three strata consisting of eight ‘equivalent’ supportive living facilities will be randomized separately to four intervention arms by first constructing two blocks of four facilities within each stratum. Using computer-generated random numbers, facilities within each block will be randomized to one of the four intervention arms. Block randomization ensures that an equal number of ‘equivalent’ facilities are assigned to each of the four arms. Research assistants will recruit clients to participate throughout the study with replacement when a client moves or dies. Clients will be eligible to participate if they can transfer independently or with the assistance of one person.

#### Blinding

Team members will be blinded to the four intervention arms with the exception of the research manager and the staff assigned to implement the reminder interventions. Research assistants implementing the reminders will be instructed to avoid discussing their work with the research team.

### Post-randomization

Immediately following randomization, a simple set of paper-based reminders will be introduced to all sites to heighten health care aides’ awareness of the sit-to-stand activity. The low intensity paper-based reminders that were tested in the MOVE study and are commonly used in clinical settings to introduce practice change, include: 1) affixing stickers to clients’ bedroom doors, beside their beds, or in their bathrooms (Additional file 2); 2) posting signs in prominent locations (Additional file 3); and 3) placing colored flags on the documentation flowsheets. Every month for the high frequency sites, and once every 3 months for the low frequency sites, the color or shape of the paper-based reminders will be modified. For the high intensity reminders, health care aides will be identified to offer peer reminders based on their demonstrated informal leadership behavior during the education sessions and in consultation with their managers. These health care aides will provide formal and informal peer reminders about the sit-to-stand activity; the formal reminders will take place either monthly or every 3 months during change of shift meetings, while the informal reminders will be provided as opportunities arise during the work day. Every month for the high frequency sites and every 3 months for the low frequency sites, the study educator will coach the health care aides providing peer reminders. To optimize the fidelity of the reminder interventions [42] leading to the primary outcome measure (health care aide uptake), a committee will be established to monitor the fidelity of the reminder interventions and recommend strategies to mitigate any identified problems.

### Measures (research questions 1 to 3)

#### Primary outcome measure

As the purpose of this study is to examine the effectiveness of reminders to support the sustainability of a mobility innovation by health care aides, the primary outcome is health care aide uptake as operationalized by the number of completed sit-to-stand occasions. In the absence of a previously developed uptake measure [48], we have validated a documentation flowsheet (Additional file 4). Health care aides will record on this flowsheet the number of sit-to-stands that the client completes on each of two occasions on the day shift and on the evening shift (that is, four occasions per day). Research staff will score the flowsheet for each occasion with ‘1’ denoting a completed occasion of sit-to-stand activity and ‘0’ denoting that the sit-to-stand activity was not completed.

The reliability and validity of these documentation flowsheets were assessed using two methods. First, 31 health care aides viewed two videotaped vignettes depicting the sit-to-stand activity, and recorded on flowsheets the number of sit-to-stands the clients performed. The exact agreement between observed and recorded number of sit-to-stands was 90.3% for the first vignette and 80.6% for the second vignette. Second, we used logistic regression to examine the relationship between the change in 26 clients’ mobility and the number of occasions that the sit-to-stand activity was completed (odds ratio = 1.07; *P* = 0.023) to assess concurrent validity. Clients that completed the sit-to-stand activity more often, as recorded on flowsheets, were more likely to either maintain or improve their ability to stand up from a chair when compared with clients that completed the activity less often.

In addition to this completed validation work, we have piloted two other validation approaches. Preliminary results from observing five clients show 87.5% exact agreement between the number of observed and recorded sit-to-stands. We also used the activPAL3 activity monitoring device (Pal Technologies, Glasgow, UK), which provides minute-by-minute information on the client’s activity. ActivPAL counts of standing and sitting repetitions in stroke patients has good exact agreement with counts by direct observation, an indication of concurrent validity [34,49]. Preliminary results using the activPAL3, to compare activity output of five clients with flowsheet records for 3 days, show 84.6% exact agreement. There was no evidence of skin irritation, and clients forgot they were wearing the device.

START will continue to assess the reliability of the flowsheets across all four treatment arms. We will compare direct observations of 28 clients (seven in each of the four treatment arms) completing the sit-to-stand activity with the number of sit-to-stands recorded by health care aides on flowsheets. Similarly we will compare the activPAL3 output of 28 clients with their flowsheet recordings. A sample size of 27 subjects yields 80% power to demonstrate excellent agreement (correlation = 0.85), assuming 0.95 for the true correlation.

#### Sample size calculation for primary outcome

The required sample size for the trial is 24 facilities, each with an average of 15 health care aides assigned to two clients. Each aide is expected to have 1,440 (2 × 2 × 30 × 12) possible uptake occasions with each client, for an expected total of 43,200 (15 × 2 × 1,440) aide-occasions per facility over the trial’s duration. The sample size calculation, based upon previous results from four facilities consisting of 44 aides [7,50], yielded an estimated non-interventional uptake rate of 22.6% with a coefficient of variation (CV) of 0.54 among facilities. The CV plays the role of the between-facility clustering parameter in the sample size formula for rates [51]. For the purpose of sample size calculations, we assume the low-low arm to have an uptake rate of 20%, the single-high arms to have an uptake rate of 55%, and the double-high arm to have an uptake rate of 90%. The additive trial design has 80% power at a 5% two-sided level of significance to detect a 93.3% relative increase in the marginal rates of uptake (72.5% versus 37.5%) between high and low (Figure 3).

**Figure 3 F3:**
[figure not shown]
Sample size assumptions.

#### Secondary outcome measure

We will also measure the sustainability of client mobility across the four intervention arms. At the end of a year of data collection, a sample of clients will be assessed using the 30-second sit-to-stand test. The sit-to-stand action is a functional activity that has been incorporated into a number of mobility measures including the time for five sit-to-stands and the number of sit-to-stands completed in 30 seconds (the 30-second sit-to-stand test). We will measure the 30-second sit-to-stand test because in our population clients may be unable to complete more than two or three sit-to-stands [37,52-54]. Using a stopwatch and a standard armchair, we will instruct client participants to stand up and sit down as many times as possible until they are asked to stop after 30 seconds. In community-dwelling older adults, there is evidence for test-retest reliability, criterion validity (chair stand performance compared with lower body strength), and discriminant validity (performance of different age and physical activity groups) with this 30-second sit-to-stand test [52].

#### Sample size calculation for secondary outcome

We expect 65% of the original 720 clients to survive, yielding 468 clients. A proposed sample size of 200 clients (50 per arm) will have 80% power at a 5% two-sided level of significance to detect an absolute mean difference of one sit-to-stand (5.5 versus 4.5) between high and low treatment arms. The calculation, based upon results from six facilities of 75 clients from the MOVE study, yielded an estimated non-interventional mean number of 4.3 (SD = 2.5) sit-to-stands with an intraclass correlation coefficient (ICC) of −0.05 within each facility. For the purpose of sample size calculation, we assume at 1-year follow-up, the low-low arm will have a mean number of sit-to-stands of four on the 30-second sit-to-stand test, the low-high and the high-low arms will have a mean number of five, and the high-high arm will have a mean number of six.

#### Pre-randomization facility assessment measures

Characteristics of supportive living facilities, health care aides, and clients will be used to describe the sample, identify ‘equivalent’ facility groups for block randomization, and add to the process evaluation.

Facility/unit characteristics include facility and unit size (bed number), facility ownership model (for-profit or not-for-profit), client-to-staff ratios, rehabilitation service availability, and organizational context (ACT) [26]. It is a reliable and valid measure of organizational context when completed by individual care providers in pediatric units [45,55] or nursing homes [56,57]. A total of 15 health care aides will complete the ACT in each participating facility. Eligible health care aides must work a minimum of six shifts per month and have worked at least 3 months in the facility.

Health care aide demographic characteristics (age, sex, education, first language, duration of employment) will be assessed, and the 9-item Utrecht Work Engagement Scale (UWES) (Additional file 5) [46,47] will be completed when the ACT is administered. The UWES assesses the work engagement dimensions of vigor, dedication, and absorption.

### Trial data management and analysis (research questions 1 to 3)

Data will be entered by a contracted agency into a statistical database (SPSS version 19; IBM, Armonk, NY, USA) programmed to minimize data entry errors. All of the data will be double entered to assess the accuracy of data entry. Research participants will be assigned unique identifiers and all personal identification will be removed before data cleaning and analysis. A graduate student will be hired to clean the data using standard data management techniques. All analyses will follow the intention-to-treat principle, namely that all participants will be included regardless of deviation from protocol. SAS 9.2 (SAS Institute, Cary, NC, USA) software will be used to perform the aide-level analyses. For the primary outcome measure, the total number of completed sit-to-stand occasions out of the total number of possible (completed and not completed aide-occasions) will be calculated. As the design is a stratified additive 2 × 2 factorial, generalized estimation equations (GEE) with a log link, Poisson distribution, an exchangeable working correlation structure, and no interaction term will be used to simultaneously test the significance of the high versus low intensity and frequency using Wald tests (PROC GENMOD). The model will include ‘equivalent’ strata as a covariate and log total aide-occasions as the offset. Robust variance estimators will be employed to adjust for the effect of clustering. Although the size of the trial is not statistically powered to detect a synergistic effect between intensity and frequency, an interaction term will be incorporated into the model to test for this effect. In the event that imbalance on baseline facility and health care aide characteristics among groups occurs, GEE naturally facilitates additional analyses to examine, and control for, their influence. Rate ratios will be used in quantifying the effectiveness of the high versus low intensity and frequency reminders. For the secondary outcome measure, a mixed effects linear regression model (PROC MIXED) will be used, with facility considered as a random effect to account for the clustering, no interaction term, and ‘equivalent’ strata and baseline sit-to-stand number as covariates. An interaction term will be incorporated into the model to test for a synergistic effect between intensity and frequency, as well as baseline facility and health care aide characteristics if unbalanced. Least squares means will be used to quantify the effectiveness of the interventions. Based on the Medical Research Council (MRC) framework for developing and evaluating complex interventions, we are moving from the pilot stage to the evaluation stage of knowledge translation interventions [43].

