### Research questions

1. Do more frequent reminders (every month) improve the sustainability of the sit-to-stand activity by health care aides in supportive living facilities compared with less frequent reminders (every 3 months)?

2. Do high intensity reminders (paper-based reminders plus peer reminders) improve the sustainability of the sit-to-stand activity by health care aides in supportive living facilities compared with low intensity reminders (paper-based reminders only)?

3. Do more frequent reminders plus high intensity reminders synergistically improve the sustainability of the sit-to-stand activity by health care aides in supportive living facilities?

4. What are the processes associated with the ongoing uptake of the sit-to-stand activity over a year of follow-up?

### Hypotheses for research questions 1 to 3

1. Arm 1 with low intensity and low frequency reminders will have poor uptake of the activity.

2. Arm 2 with low intensity and high frequency reminders will have moderate uptake of the activity.

3. Arm 3 with high intensity and low frequency reminders will have moderate uptake of the activity.

4. Arm 4 with high intensity and high frequency reminders will have excellent uptake of the activity.

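### Uptake is planned as additive in percentage points, but synergy is tested on a log scale, where the plan's own no-synergy rates read as antagonism

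*Protocol article*

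**What the plan says.** The section on sample size for the primary outcome states "we assume the low-low arm to have an uptake rate of 20%, the single-high arms to have an uptake rate of 55" per cent, and "the double-high arm to have an uptake rate of 90" per cent. It calls the design additive and claims "80% power at a 5% two-sided level of significance to detect a 93.3% relative increase in the marginal rates of uptake", that is, 72.5% against 37.5%.

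The section on trial data management and analysis gives the additive factorial design as the reason for "generalized estimation equations (GEE) with a log link, Poisson distribution, an exchangeable working correlation structure, and no interaction term". Results for each factor are to be rate ratios. The section concedes that the trial is not powered for synergy, but says that "an interaction term will be incorporated into the model to test for this effect".

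Research question 3 asks: "Do more frequent reminders plus high intensity reminders synergistically improve the sustainability" of the activity? The section on expected outcomes lists the answer among the things that will be known when the study ends. The article never names the scale on which it means additive or synergistic.

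**The concern.** Whether two factors interact depends on the scale. Effects that add in percentage points generally do not multiply, and the gap is large when rates run from 20% to 90%. The planning figures contain no synergy on the percentage-point scale. The test asks a different question: whether the double-high arm exceeds the product of the two separate rate ratios. If uptake came out as planned, research question 3 would be answered with the wrong sign, and a combination that delivered its full expected benefit could be reported as one whose components undermine each other. The trial is meant to say which combination of frequency and intensity works best, so this matters for its message even though the synergy test is secondary.

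**Working it through.** **Inputs.** From the sample size section: arm rates 0.20, 0.55, 0.55, 0.90; between-facility CV k = 0.54; 24 facilities; 43,200 aide-occasions per facility. From the randomization section: equal allocation, so 6 facilities per arm and 12 per factor level.

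**1. The plan's own figure.** Marginal rates are (0.55 + 0.90)/2 = 0.725 and (0.20 + 0.55)/2 = 0.375. Their ratio is 1.933, the stated 93.3% increase. The usual cluster-rate formula gives, per factor level,
(1.96 + 0.84)² × [(0.375 + 0.725)/43,200 + 0.54² × (0.375² + 0.725²)] / 0.35² = 12.45 facilities.
With 12 per level, power is 78.5%, close to the stated 80%. The plan's figure is reproduced.

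**2. Interaction at the planned rates.**
- Difference scale: 90 − 55 − 55 + 20 = 0 points.
- Log scale: 0.90 × 0.20 / (0.55 × 0.55) = 0.595 (log −0.519).
- Double-high rate needed for a log-scale ratio of 1: 0.55²/0.20 = 151%, which is impossible.
- Double-high uptake of 100%: 1.00 × 0.20/0.55² = 0.661.

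So with single-high arms at 55%, every more-than-additive result (90% to 100%) has a log-scale ratio between 0.595 and 0.661.

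**3. Where a positive log-scale result is possible.** With low-low at 20% and equal single-high rates s, the ratio exceeds 1 only if s² < 0.20 × double-high rate.
- Double-high 90%: s < √0.18 = 42.4%.
- Double-high 100%: s < √0.20 = 44.7%.
- At 20/30/30/90 the ratio is 2.0.
- At s = 40%, additivity predicts 60% and multiplicativity 80%. A double-high rate between these is more than additive, yet still has a ratio below 1.

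**4. How often the wrong sign would be significant (planned rates true).** With CV 0.54 in every arm, the standard error of the log interaction is √(4 × 0.54²/6) = 0.441. Then:
- P(significant antagonism) = Φ(−1.96 + 0.519/0.441) = 22%.
- P(significant synergy) = 1 − Φ(1.96 + 0.519/0.441) = 0.1%.

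A CV of 0.54 is not attainable at 90%, where the maximum is √(0.10/0.90) = 0.333. Simulations with beta-distributed facility rates and a feasible spread in that arm gave significant antagonism in 23% (small-sample-corrected t test), 27% (CV 0.25 in the double-high arm, uncorrected) and 31% to 34% (capped at the feasible spread, uncorrected). Significant synergy stayed well under 1%.

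**5. Main-effects model.** Fitted to the planned rates with equal arms, a(1 + r) = 0.75 and ar(1 + r) = 1.45, so r = 1.933 and a = 0.256. Fitted arm rates are 25.6/49.4/49.4/95.6% against 20/55/55/90%. The ratio r is the powered marginal contrast. The planned simple effects are 0.55/0.20 = 2.75 with the other factor low and 0.90/0.55 = 1.64 with it high.

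**6. Comparison within the article.** The secondary outcome is planned at 4/5/5/6 sit-to-stands (6 − 5 − 5 + 4 = 0) and analysed by linear regression, so planning and testing share a scale there. Only the primary outcome has the mismatch.

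**The case against.** The strongest reply is that the primary analysis is coherent. The target is stated as a relative increase in marginal rates, the result is a rate ratio, and with equal arms the model returns exactly that marginal ratio. Additive can be read simply as a main-effects model, and choosing ratios over differences is legitimate. This stands. A reader might infer that the single rate ratio describes no real contrast, or that the main-effect tests fail. The figures do not support either.

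A reader might also infer that research question 3 can never come out positive. That is too strong. The arm rates are given only for sample size purposes, the observed non-interventional rate was 22.6%, and step 3 shows that smaller single-factor effects leave room for a positive result.

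A third inference is that the informal peer reminders ("while the informal reminders will be provided as opportunities arise during the work day") would weaken the frequency effect in the peer arms. No figure in the article supports this, and the point does not need it.

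The admission that synergy is not powered does not answer the concern. Low power means that a true effect may be missed. Here the estimate itself points the other way.

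Finally, the ceiling also limits the remedy. At 20/55/55 the largest possible synergy is 10 points. By normal approximation, a double-high rate of 99% would be detected on the difference scale with power of about 7% (CV 0.54, capped), 15% (facility SD 0.122) or 28% (SD 0.08). That is conceded: the remedy corrects the meaning and sign of the test, not its power.

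**Conclusion.** The point holds for research question 3. The planning scale and the scale of the synergy test do not match, and at the plan's own rates a no-synergy truth gives a tested ratio of 0.595. Significant antagonism would appear in roughly 22% to 34% of trials at CV 0.54, and significant synergy in well under 1%. The direction follows from the arm rates alone. The percentages also assume 6 facilities per arm, a feasible spread in the 90% arm and a choice of small-sample method. Smaller facility SDs give higher percentages (54% to 57% at SD 0.122, 85% to 86% at SD 0.08), but the protocol states no such SDs for these arms, so the conclusion does not rest on them.

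The distortion applies at and near the planned rates. It shrinks if single-factor effects are small: at 20/30/30, additivity predicts 40% and multiplicativity 45%. The powered main-effect tests, the stated sample size and the 1.933 ratio are not undermined (equality with the marginal ratio assumes facilities of equal size). What the single ratio does is hide simple effects of 2.75 and 1.64. This should be corrected, but it does not threaten the primary analysis.

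**What to change.** In the analysis section, define synergy as departure from additivity in the uptake proportion. Test the interaction on the difference scale, for example by facility-level linear regression of uptake on intensity, frequency, their product and stratum, or by an interaction contrast standardised from the four arm rates. Keep the log-link rate ratios for the main effects. Beside them, report the four arm-specific rates and the effect of each factor at each level of the other.

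This costs a change of wording and one extra analysis, with no new data. The synergy test remains underpowered, and the report should say so. The trial status section records 2 of 24 facilities and no residents recruited, so the change can be made before any outcome data exist.

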### Pre-randomization

The purpose of the pre-randomization period is to prepare for randomization by: 1) facility assessments to identify three ‘equivalent’ groups of facilities to be randomized across the arms; 2) sit-to-stand education sessions to establish initial adoption of the mobility innovation; and 3) uptake monitoring to ensure the primary outcome measure, uptake of the innovation, is operational in each facility.

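### The primary model makes no use of the two months of pre-randomisation uptake, although the secondary model adjusts for its own baseline; this gives up precision, not validity

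*Protocol article*

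**What the plan says.** - **Baseline uptake is collected.** Under Pre-randomization, one of the three aims is "uptake monitoring to ensure the primary outcome measure, uptake of the innovation, is operational in each facility". Under Uptake monitoring, the team states that "we will monitor uptake and enhance the reliability of the health care aides’ flowsheet documentation for 2 months prior to randomization". The same section adds: "Flowsheets for each participant will be collected at the end of every month".
- **It is the primary outcome.** Under Primary outcome measure, "the primary outcome is health care aide uptake as operationalized by the number of completed sit-to-stand occasions", scored from the flowsheet.
- **The primary model leaves it out.** Under Trial data management and analysis, the model has the two factors without interaction, "strata as a covariate and log total aide-occasions as the offset".
- **The secondary model takes its own baseline.** The same section lists "strata and baseline sit-to-stand number as covariates" for the 30-second sit-to-stand test.
- **Imbalance is handled differently for the two outcomes.** For the primary outcome: "In the event that imbalance on baseline facility and health care aide characteristics among groups occurs, GEE naturally facilitates additional analyses". For the secondary outcome, baseline facility and aide characteristics are added to the model itself if they turn out unbalanced.
- **Strata.** Facility assessment forms them from the context tool and the work-engagement survey. Pre-randomization facility assessment measures allows wider facility, aide and client characteristics to identify the groups. Neither section names early uptake.

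**The concern.** Each facility contributes an expected 43,200 aide-occasions, so nearly all the uncertainty in a facility's rate comes from differences between facilities. A facility's uptake before randomisation, measured with the same instrument, is a natural candidate for explaining part of that spread. The protocol also defines sustainability as continued use after initial adoption efforts end, so the level reached at initial adoption is a sensible reference point.

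At stake is the precision of both main effects, and protection against a chance difference in initial adoption when each arm has six facilities. The planned effect is very large (37.5% versus 72.5%), so a smaller detectable ratio would matter if the true effect is more modest.

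This is not a detail lost through condensation. The article spells out the link, distribution, working correlation, covariate and offset of the primary model, and it includes a baseline value for the other outcome in the same paragraph.

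**Working it through.** **Inputs from Sample size calculation for primary outcome:** 24 facilities, hence 12 per level of each factor; marginal rates 0.375 and 0.725; CV 0.54; 43,200 occasions per facility; 5% two-sided; 80% power. **Assumed:** r, the facility-level correlation of baseline with follow-up uptake given strata. The article gives no figure, so a range is shown.

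**1. Reproduce the stated power.** Cluster formula for rates, without the optional extra cluster per level:

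- Variance term = (0.375 + 0.725)/43,200 + 0.54² × (0.375² + 0.725²) = 0.0000255 + 0.19428 = 0.19430.
- z = 0.35 × √(12/0.19430) − 1.96 = 2.751 − 1.960 = 0.791, so power is 78.5%.
- Facilities per level for 80%: (1.960 + 0.842)² × 0.19430/0.35² = 12.45.

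This agrees with the stated 80% within tolerance. With the extra cluster per level, power is 75.0%. The first variance component is about 0.01% of the total, so between-facility spread determines the standard error.

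**2. Effect of a baseline covariate, log scale.** This matches the log link of the planned model. A t reference is used to be cautious with 24 clusters.

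- log(0.725/0.375) = 0.659.
- Unadjusted SE = √(2 × 0.54²/12) = 0.2205.
- Adjusted SE = 0.2205 × √(1 − r²).
- Degrees of freedom: 24 − 1 − 2 factors − 2 strata = 19 unadjusted; 18 with the covariate.

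| r | Residual variance removed | SE | Power for ratio 1.93 | Ratio detectable at 80% |
|---|---|---|---|---|
| none | 0% | 0.2205 | 81% | 1.92 |
| 0.2 | 4% | 0.216 | 82% | 1.90 |
| 0.3 | 9% | 0.210 | 84% | 1.86 |
| 0.5 | 25% | 0.191 | 90% | 1.76 |
| 0.7 | 49% | 0.157 | 98% | 1.59 |

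**3. Cross-check with the rate formula of step 1,** replacing 0.54 by 0.54 × √(1 − r²): power is 78.5% unadjusted, then 80.2%, 82.2%, 88.8% and 97.1% for r = 0.2, 0.3, 0.5 and 0.7. The level differs but the pattern is the same.

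**4. Size of chance differences.** A chance deviation of one standard error multiplies the estimated rate ratio by exp(0.2205) = 1.25. Adjustment removes the part of this that baseline uptake predicts.

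**The case against.** The strongest reply is that nothing here is an error. Randomisation makes the strata-adjusted comparison valid, power was planned without the covariate, and chance imbalance in initial adoption is already part of the variation that the standard error reflects. All of that stands.

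The gain may also be smaller than the table suggests, for four reasons:

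- The relevant r is the partial correlation given strata. The strata may draw on facility size, ownership, staffing ratio and rehabilitation services as well as the two surveys. The calculation charges degrees of freedom for strata but credits them with no variance reduction.
- The two months are a supported run-in, with flowsheet correction, walkabouts and documentation sessions. Reminders start only after randomisation.
- Clients are replaced when they move or die, and only 65% of the original clients are expected to survive.
- Constant CV cannot hold near the planned 90% rate: 0.54 × 0.90 gives an SD of 0.49, but a proportion with mean 0.90 cannot have an SD above √(0.9 × 0.1) = 0.30.

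These points make the figures upper-side. They do not make a covariate measured before allocation invalid.

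Three stronger readings are tempting but unsupported. A reader might infer that the treatment estimate is biased, or that a high rate under one reminder level could simply reflect facilities that started high; the comparison is between randomised groups, so this is random error covered by the standard error. A reader might infer that the stated power is wrong; it reproduces. A reader might infer that observed imbalance selects the primary model; the text places that adjustment in additional analyses and keeps the primary model fixed.

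**Conclusion.** The point holds as a missed gain in efficiency. The article collects a baseline of the primary outcome in every facility, adjusts the secondary outcome for its baseline, and gives no reason for treating the primary outcome differently. The benefit ranges from about 1 percentage point of power at r = 0.2 to about 17 at r = 0.7 on the log scale, with the detectable ratio falling from 1.92 to between 1.90 and 1.59. The conclusion that the data go unused rests on the text alone. The size rests on an assumed correlation, a constant CV of 0.54 and no variance reduction from strata, so no single value should be quoted as the expected gain.

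The criticism of imbalance-triggered adjustment applies to the secondary model only. There, observed imbalance decides which facility and aide characteristics enter, regardless of how prognostic they are.

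**What to change.** - **Primary model:** prespecify each facility's uptake rate over the two monitored months, for example on the log scale, as a fixed covariate in the GEE model regardless of observed imbalance. If the team considers the run-in data unsuitable, say why.
- **Primary outcome, imbalance:** keep the imbalance-triggered analyses as the additional (sensitivity) analyses they already are.
- **Secondary model:** fix the covariates of the main reported model in advance, and move any adjustment prompted by imbalance to sensitivity analyses.

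The cost is a sentence or two and one facility-level degree of freedom (19 to 18). No new data are needed, and allocation cannot affect the covariate. Under Trial status, 2 of 24 facilities and no clients had been recruited, so at that stage the change could be made before any outcome data existed.
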